#### Pre-target quit date assessment

Three days before their target quit date, participants will be sent a link to complete questionnaires to assess their recent mood (PHQ-9 [18] and PANAS-SF [19]), nicotine withdrawal symptoms (MNWS [20]), and level of perceived stress (PSS-4 [21]).

#### Treatment intervention (6 weeks)

Participants will undergo 6 weeks of NRT treatment with access to additional behavioral support via videos and My Change Plan smartphone app. The timing of the start of NRT to a particular menstrual cycle phase is part of the intervention.

#### Follow-up period (6 months)

At 6 months post-target quit date, participants will complete a follow-up questionnaire regarding current smoking status and smoking behavior since study participation to capture the incidence of lapse and relapse. If they self-report abstinence for at least 7 days, they will be mailed a fourth dried blood spot kit, asked to collect the dried blood spot, and mail it within 3 days of collection. For a schematic presentation of the participant timeline, refer to Fig. 2.

### Sample size {14}

We estimate 1200 participants (1:1:1 allocation ratio) to be a realistic sample size, allowing us to achieve sufficient statistical power for the primary outcome analysis. To evaluate power for the primary objective, we ran simulations at various sample sizes by randomly generating data using distributions and coefficients drawn from existing data from the STOP Program. To confirm the final sample, we ran a set of 10,000 simulations. A total analysis sample of 1200 participants allocated in a 1:1:1 ratio using simple randomization will provide 80% power to detect a statistically significant difference for our primary outcome. We anticipate that the proportions quitting successfully on day 7 post-TQD will be 25% in the usual practice group, 34% in one intervention arm, and 25% in the other intervention arm. The effect sizes were calculated without accounting for attrition in the final sample size.

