### Trial design {8}

The study design is an open-label, parallel-group, superiority randomized controlled trial. Participants will be randomized into three groups in a 1:1:1 allocation ratio: (1) quit smoking during the mid-luteal phase of their menstrual cycle (6–8 days pre-onset of menses), (2) quit smoking during the mid-follicular phase of their menstrual cycle (6–8 days post-onset of menses), or (3) quit smoking 15–30 days post-enrollment with no regard to the menstrual cycle phase (usual practice). All participants will receive 6 weeks of NRT to aid in their quit attempt. The expected duration of the clinical trial is 48 months; we expect participant recruitment and data collection to occur over 27 months. Participants are not required to make any in-person visits; therefore, any potential COVID-19 restrictions are not expected to cause any significant disruptions to our timeline.

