### Eligibility criteria {10}

#### Inclusion criteria

The study will recruit 1200 treatment-seeking naturally cycling individuals within Ontario, with a regular menstrual cycle (defined as cycle length ranging from 21 to 35 days over the past 6 months) aged 18 to 40 years. Eligible individuals must smoke at least 5 cigarettes per day over the past 6 months, be willing to quit smoking using NRT (nicotine patches and nicotine gum or lozenge) within 30 days and to make a quit attempt on their assigned target quit date, be willing to comply with study procedures (including providing dried blood spots), and provide a valid e-mail address to receive essential study communication and invitations to complete follow-up questionnaires.

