## Statistical methods

### Statistical methods for primary and secondary outcomes {20a}

#### Primary analysis

To evaluate the primary outcome, we will compare the proportions of biochemically abstinent participants between the groups. Consistent with current practice, and because we expect an advantage over usual practice for only one menstrual cycle phase group, we will compare each intervention arm to usual practice without adjustment for multiplicity. A *p*-value < 0.05 will be considered statistically significant.

We will use logistic regression to test the group differences. As adjustment for prognostically important baseline covariates increases power and decreases bias, we will adjust for age, income, and the heaviness of smoking index (HSI), all of which are known to be meaningfully predictive of successful smoking cessation. We will fit two separate models [26], one for each of our comparisons (i.e., follicular phase group vs. usual practice group and luteal phase group vs. usual practice group).

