### Methods in analysis to handle protocol non-adherence and any statistical methods to handle missing data {20c}

We anticipate minimal missing data (< 5%) for the primary outcome (day 7 smoking status) due to our daily contact with participants during the treatment phase. We will evaluate the effects of missingness by calculating differences across plausible and extreme missing-data scenarios. If our primary test is significant, we will also calculate the size of the interaction between the group and missingness that would be required to make this difference non-significant. If missing data causes the exclusion of 10% or more of the baseline sample, we will conduct an analysis using multiple imputation. In our imputation models, we will include the variables from our primary analysis, biochemically verified quit status, data on craving, and NRT use at all available time points.

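### The stated 80% power holds only if all 1200 recruits are analysed and usual practice is exactly 25%; the protocol allows for no loss and leaves unstated the assumption that reconciles its three rates

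*Protocol article*

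**What the plan says.** - **Power claim.** Protocol article, Sample size {14}: "A total analysis sample of 1200 participants allocated in a 1:1:1 ratio using simple randomization will provide 80% power", from 10,000 simulations based on data from the group's existing cessation programme (STOP). The assumed day-7 rates are "25% in the usual practice group, 34% in one intervention arm, and 25% in the other intervention arm".
- **Loss.** The same section discloses: "The effect sizes were calculated without accounting for attrition in the final sample size". Inclusion criteria: "The study will recruit 1200 treatment-seeking naturally cycling individuals within Ontario", the same number as the analysis sample. Section {20c}: "We anticipate minimal missing data (< 5%) for the primary outcome (day 7 smoking status", with multiple imputation if 10% or more of the baseline sample would be excluded. Section {18b} does not retain the data of participants who withdraw, or who are withdrawn for missing the week 1 and week 6 assessments. The Discussion names loss to follow-up as a possible limitation.
- **Comparator timing.** Trial design {8}: the third group quits 15–30 "days post-enrollment with no regard to the menstrual cycle phase (usual practice"). The two phase arms use three-day windows, 6–8 days before or after the onset of menses.
- **Test.** Primary analysis: "we will compare each intervention arm to usual practice without adjustment for multiplicity"; a p-value below 0.05 "will be considered statistically significant". The models adjust for age, income and the heaviness of smoking index.

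**The concern.** Two inputs to the power claim sit badly with the rest of the protocol.

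1. The 80% belongs to 1200 analysed participants, but 1200 is also the number enrolled. Any missing day-7 outcome or discarded record takes the trial below the sample on which the claim rests.

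2. Usual practice is given the same 25% as the phase arm expected to show no advantage. Yet its quit dates are spread over a 16-day range (days 15 to 30) in people whose cycles last 21 to 35 days, so some will fall at the favourable time by chance. If quitting at that time yields 34%, a group average of 25% requires the remaining dates to average below 25%. The protocol does not say this, nor does it say why the other phase arm should still be at 25%.

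At stake is how far the stated power can be trusted for the comparison that defines success, a phase arm against usual practice. How much it changes depends on which of the three rates is the firm one.

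**Working it through.** **Inputs from the protocol.** Rates 25%, 34%, 25%; 1200 analysed at 1:1:1, so 400 per arm; level 0.05 per comparison with no multiplicity adjustment; missing primary outcome below 5%; imputation trigger at 10%.

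**Assumptions added here.** A two-sided test: sidedness is not stated, but two-sided reproduces the 80%, whereas one-sided gives 87.5%. Also f, the share of usual-practice quit dates at the favourable time, which the protocol does not give. The range shown runs from 3/28 (benefit only in a three-day window of a 28-day cycle) to 0.5 (benefit throughout half the cycle).

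**Formula.** Two proportions, pooled variance under the null:

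power = Φ[(p₁ − p₀ − 1.96·s₀)/s₁], with s₀ = √[2p̄(1 − p̄)/n], s₁ = √{[p₀(1 − p₀) + p₁(1 − p₁)]/n} and p̄ = (p₀ + p₁)/2.

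**Step 1: reproduce the 80%.** With p₀ = 0.25, p₁ = 0.34 and n = 400, s₀ = 0.03225 and s₁ = 0.03209, so power = Φ[(0.09 − 0.06320)/0.03209] = Φ(0.835) = 79.8%. The unpooled variant gives 80.1%. A 200,000-run simulation with simple randomization of 1200 gives 79.9%. The stated figure is correct for its inputs.

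**Step 2: loss only (25% vs 34%, complete cases, unadjusted).**

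| Loss | n per arm | Power |
|---|---|---|
| 0% | 400 | 79.8% |
| 5% | 380 | 77.8% |
| 10% | 360 | 75.5% |

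**Step 3: reading A, dates outside the favourable time yield 25%.** The usual-practice rate is 0.34f + 0.25(1 − f) = 25% + 9f points. Power of the favourable arm (34%) against it:

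| f | Usual practice | Power, 400 per arm | Power, 380 per arm (5% loss) |
|---|---|---|---|
| 3/28 | 26.0% | 69.9% | 67.7% |
| 0.25 | 27.25% | 54.4% | 52.3% |
| 0.5 | 29.5% | 27.6% | 26.5% |

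**Step 4: reading B, 25% is a true mixed-phase rate.** Power against usual practice is then as in steps 1 and 2, near 80% before loss. The other dates must average x = (0.25 − 0.34f)/(1 − f):

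- f = 3/28: (0.25 − 0.0364)/0.8929 = 23.9%
- f = 0.25: (0.25 − 0.085)/0.75 = 22.0%
- f = 0.5: (0.25 − 0.17)/0.5 = 16.0%

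The first value is easy to reconcile with 25% in the other three-day window. The last is not, without an explanation.

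**Step 5: the two phase arms against each other.** Simulated under reading A with f = 0.5 (29.5%, 34%, 25%), this contrast keeps 79.9% power. Under reading B with f = 0.5 (25%, 34%, 16%) it has more than 99%.

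**The case against.** The strongest reply is that nothing has been miscalculated and that the fraction f comes from outside the protocol. The simulations drew on STOP data, and nothing in the article says quit dates there were timed to the cycle. The Background reports 24% quit success for women in that programme. The article does not tie that figure to the 25%, but a mixed-phase origin is plausible. In that case reading B applies, power against usual practice stays near 80%, and the doubtful input is the other arm's 25%, which does not enter that contrast. The 34% and 25% also refer to three-day windows, and with benefit confined to such a window the remaining dates need be only about one point lower. All of this stands, and it is why the 28% to 70% figures can be offered only as conditional.

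The loss limb is also modest. The omission is disclosed, the cost at the protocol's own 5% bound is about two points, and the 10% row ignores the planned imputation. Covariate adjustment, which the protocol says increases power, cannot be rerun because the coefficients are not given.

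Two stronger readings are tempting, and the documents support neither:

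- **That the 80% is wrong, or that the trial really has 28% to 55% power.** The figure reproduces, and the low values need both reading A and a value of f that the protocol does not supply.
- **That a null primary result would be taken to mean phase timing is irrelevant.** No section says so. Section {6b} explains why a benefit over usual practice is the question. If many usual-practice participants already quit at the favourable time, targeting truly gains less, and the trial would measure that. The follicular-versus-luteal contrast at day 7 is already prespecified in the Objectives, Secondary outcomes and Secondary analyses.

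**Conclusion.** The concern holds as one about inputs and disclosure, not arithmetic. The 80% is right for 1200 analysed participants and a usual-practice rate of exactly 25%. Recruiting 1200 with no allowance does not provide the first condition: unadjusted complete-case power is 77.8% at 5% loss and 75.5% at 10%.

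The set 25/34/25 is coherent only if almost no usual-practice date is favourable, or if other cycle days fall below 25%; the protocol states neither. Depending on which rate is held firm, either power against usual practice falls (about 70%, 54% or 28% for f = 3/28, 0.25 or 0.5), or power stays near 80% and the other dates average about 24%, 22% or 16%. The protocol does not allow a choice between these. The conclusion is therefore that the assumption must be stated, not that the power is any particular lower number.

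**What to change.** Revise Sample size {14} in three respects:

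1. Give power for the number expected to be analysed, at the protocol's 5% missing-data bound and at its 10% imputation trigger, beside the figure for 1200. Say whether records discarded under section {18b} count towards the loss.
2. State whether the 25% for usual practice is a mixed-phase rate or the rate at unfavourable times. If mixed-phase, justify 25% for the other phase arm; if not, set usual practice to match the expected share of favourable dates.
3. Rerun the existing simulation, with its covariates, over a stated range of f (for example 0.1 to 0.5), and present it as a sensitivity analysis conditional on that assumption.

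The cost is a rerun of existing code, a short paragraph and a less favourable stated power. No additional participants and no change to the primary comparison are required.

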### Recruitment {15}

The Nicotine Dependence Clinic at CAMH offers in-person and online smoking cessation programs and will be one source of referral to the study. Our STOP on the Net online smoking cessation program enrolls 1500–2000 participants per month, on average, which includes 300–400 self-identified women aged 18–40, illustrating the feasibility of recruiting 1200 eligible women over 2 years to participate in this study. The trial will be posted on the public CAMH website including the “CAMH Find a Study online” where individuals can explore studies that they may be interested in participating in. In addition, participants can learn about the study through online postings (i.e., Google Ads, Facebook, Twitter, Instagram) and word-of-mouth. In total, we expect to enroll at least 70 eligible participants per month and have the capacity to enroll as many as 200 per month.

### Assignment of interventions: allocation

#### Sequence generation {16a}

Given the large sample size, the need to assign groups at the time of enrollment, and the expense and complexity of implementing more complex strategies in an online platform, we will allocate participants to treatment groups using simple randomization, implemented through the randomization module in REDCap. Randomization parameters were defined, and an allocation table was developed by the study team outside of REDCap.

#### Concealment mechanism {16b}

Randomization of each participant will occur shortly after their enrollment. Participants will not be directly informed of their group assignment; however, they will be provided with a date range for their target quit date to prepare for their quit attempt and the start of the intervention. The allocation sequence will be uploaded to REDCap and will be protected by restricting user rights so it will only be accessible to the study statistician and data manager, who are not involved in recruitment. Therefore, the sequence will be concealed from both participants and unauthorized study staff.

#### Implementation {16c}

The allocation sequence will be generated using a computer application for random number generation and uploaded to REDCap. Following enrollment of eligible participants (upon completion of the informed consent form and screening questionnaire), the research staff will allocate each participant to a group using the REDCap randomization module.

### Assignment of interventions: blinding

#### Who will be blinded {17a}

This study is open-label. However, the data analysis and outcome adjudication will be blinded.

#### Procedure for unblinding if needed {17b}

Once the analysis of the primary and secondary outcomes is complete, the identity of the three groups will be revealed.

### Data collection and management

#### Plans for assessment and collection of outcomes {18a}

Quit status at day 7, week 6, and 6 months post-target quit date will be assessed using REDCap questionnaires designed by the research team (see Additional file 1). These repeated assessments at different time points will allow us to track the participants’ quit status longitudinally and assess both short- and long-term outcomes. If a participant reports abstinence from smoking, their abstinence will be confirmed biochemically using dried blood spot analysis. Collecting dried blood spots is minimally invasive, cost-effective, and ideal for home sampling when conducting population-based research [22]. Filter paper blood collection demonstrates the same level of precision and reproducibility as standard methods of collecting blood [23], and the results are precise for cotinine [24], progesterone, and estradiol [25]. Additionally, the participants will be directed to complete daily diaries designed by the research team in REDCap (see Additional file 2) to provide data about their day-to-day smoking status and NRT use. The participants will also complete baseline and weekly standardized assessments of mood (PHQ-9 [18] and PANAS-SF [19]), nicotine withdrawal symptoms (MNWS [20]), and perceived stress (PSS-4 [21]). An analysis plan for daily diaries and standardized assessments is currently being developed.

#### Plans to promote participant retention and complete follow-up {18b}

Participant retention will be promoted through regular email and SMS reminders to complete study assessments. Completion of dried blood spot assessments will be encouraged through compensation in the form of $5 e-gift cards for each submitted dried blood spot. We expect to see some missing data, which will be accounted for in the statistical analysis. If a participant demonstrates significant non-adherence (defined as failure to complete week 1 and 6 questionnaires and provide dried blood spots at these time points, if required), they will be withdrawn from the study, and their data will not be retained. If a participant withdraws from the study voluntarily, a reasonable effort will be made to determine the reason for withdrawal; their data will not be retained.

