The research team will mail each participant a study kit consisting of a 6-week supply of NRT (patches plus gum or lozenge) and dried blood spot collection kits. Participants who smoke 10 or more cigarettes per day will receive 4 weeks of 21 mg and 1 week each of 14 mg and 7 mg nicotine patches, while those smoking 5–9 cigarettes per day will receive 4 weeks of 14 mg and 2 weeks of 7 mg nicotine patches. Nicotine patches will be pre-organized into weekly packages, requiring the participants to reduce the dosage from 21 mg or 14 mg to 7 mg throughout the 6-week treatment period. All groups will be instructed to collect a dried blood spot and start using their NRT on their target quit date, as well as attempt to be completely abstinent from smoking starting from their target quit date onwards. Dried blood spots will be used to measure blood cotinine levels to confirm participants’ smoking status. Participants will be instructed to apply a new patch every day and use 2 mg nicotine gum or lozenge as needed to curb any urges to smoke. The research team will provide each participant with 2 packs of nicotine gum in which the maximum dosage is 30 pieces a day. These combinations and dosages of NRT have been found most effective for smoking cessation [17].

Participants will also have access to the behavioral support videos and handouts from the time they receive their welcome e-mail until the end of the study. Participants will be asked to complete daily diaries and weekly questionnaires to document tobacco use, NRT use, nicotine craving and withdrawal symptoms, mood, adverse events, and menstrual cycle symptoms via online REDCap surveys. Additional questionnaires will include Patient Health Questionnaire [18] (PHQ-9; weeks 1 and 6), Positive Affect and Negative Affect Schedule – Short Form [19] (PANAS-SF; weeks 1–6), Minnesota Nicotine Withdrawal Scale [20] (MNWS; weeks 1–6), and Perceived Stress Scale 4 [21] (PSS-4; weeks 1–6). Smoking status will be assessed at the end of weeks 1 and 6; those who self-report continuous abstinence from smoking for at least 7 previous days will be asked to collect dried blood spots and mail them within 3 days of collection (for biochemical verification of abstinence). At the end of treatment (week 6), participants will also be asked to complete a study satisfaction survey. Refer to Fig. 1 for a brief overview of the study and to Fig. 2 for a detailed schedule of events.

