### Outcomes {12}

#### Primary outcome

We are primarily interested in the between-group comparison of proportions of biochemically confirmed abstinence, measured through dried blood spots, at 7 days post-target quit date. The trial will be considered successful if the proportion of abstinent participants in either of the groups with a target quit date based on the menstrual cycle phase (follicular or luteal) is significantly higher than in the usual practice group.

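### Two rules applied after randomisation discard the data of non-responders and of everyone who withdraws, in conflict with the article's own retention and missing-data plans

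*Protocol article*

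**What the plan says.** The section on retention and complete follow-up {18b} contains two discard rules, both acting after randomisation.

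- **Non-adherence.** Participants showing significant non-adherence, "defined as failure to complete week 1 and 6 questionnaires and provide dried blood spots at these time points, if required", are removed: "they will be withdrawn from the study, and their data will not be retained".
- **Voluntary withdrawal.** Here "a reasonable effort will be made to determine the reason for withdrawal; their data will not be retained". No time limit is given.

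The same section also says that some missing data are expected and will be dealt with in the analysis.

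Four other sections bear on these rules:

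- Primary outcome: "between-group comparison of proportions of biochemically confirmed abstinence, measured through dried blood spots, at 7 days post-target quit date".
- Intervention description {11a}, on the week 1 and week 6 checks of smoking status: "those who self-report continuous abstinence from smoking for at least 7 previous days will be asked to collect dried blood spots". Self-reported smokers are not asked for a spot at those times.
- Data management {19}: the principal investigator keeps all study data for at least 10 years.
- Missing data {20c}: under 5% missing is expected for the primary outcome. Plausible and extreme scenarios are planned, as is a calculation of how strong a group-by-missingness interaction would have to be to overturn a significant result. Then: "If missing data causes the exclusion of 10% or more of the baseline sample, we will conduct an analysis using multiple imputation".

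The article does not say that all randomised participants are analysed, or how an absent day-7 outcome is classified.

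**The concern.** Non-adherence is defined by failure to supply the outcome assessments themselves. Because a blood spot is required only from people who report abstinence, the condition also depends partly on the reported outcome. Removal on that basis is not independent of the endpoint, and it takes place after allocation.

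The withdrawal rule goes further. Someone with a verified day-7 result who leaves the study in month 3 loses that result.

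Two things are at stake. The first is the comparison of groups as randomised. The second is the means of checking how far missing data could have moved it. An analysis plan can add detail to a protocol, but it cannot bring back records that were not kept.

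**Working it through.** **1. The article's own figure.** Sample size {14} gives 80% power for 34% against 25% with 1200 participants in a 1:1:1 ratio, about 400 per arm. Two-sided alpha of 0.05 is assumed, since sidedness is not stated. The pooled standard error is s0 = 0.0322 and the unpooled one is s1 = 0.0321. Power = Φ[(0.09 − 1.96 × 0.0322)/0.0321] = Φ(0.835) = 79.8%. The stated figure reproduces. It makes no allowance for attrition: random deletion in every arm would leave 77.8% power at 5% loss and 75.5% at 10%.

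**2. Who is removed.** The phrase about weeks 1 and 6 can be read in two ways.

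| Reading | Removed | Kept |
|---|---|---|
| Failure at both times | People with no week 1 and no week 6 assessment | People missing week 1 only, to whom {20c} still applies |
| Failure at either time | Also people with a valid day-7 result who miss week 6 | Only those complete at both times |

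On both readings, complete non-responders and all voluntary withdrawers disappear.

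**3. Effect on the 10% trigger.** As an illustration, let 10% of the 1200 be deleted (120) and a further 5% of the 1200 (60) be retained with a missing outcome. Against all randomised, exclusion is 180/1200 = 15%, which triggers imputation. Against retained records it is 60/1080 = 5.6%, which does not. The article does not say which denominator applies once records are gone.

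**4. Effect on the estimate.** The discard fractions d are assumptions, as is the premise that everyone discarded is not abstinent. Observed rate = p/(1 − d), on n = 400(1 − d). The rejection probability is that of the two-sample test of proportions at ±1.96 s0.

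Example, no true effect (25% in both arms), d = 15% in the phase arm and 5% in usual practice:

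- Phase arm: 0.25/0.85 = 29.4%, n = 340.
- Usual practice: 0.25/0.95 = 26.3%, n = 380.
- Difference 3.1 points; unpooled standard error 0.0335; shift about 0.92 standard errors; rejection probability about 15%.

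| Discarded: usual practice / phase arm | Observed rates | Spurious difference | Type I error |
|---|---|---|---|
| 5% / 5% | 26.3% / 26.3% | 0 | 5.0% |
| 10% / 10% | 27.8% / 27.8% | 0 | 5.0% |
| 2.5% / 5% | 25.6% / 26.3% | +0.7 points | 5.5% |
| 0% / 5% | 25.0% / 26.3% | +1.3 points | 7.1% |
| 5% / 10% | 26.3% / 27.8% | +1.5 points | 7.3% |
| 5% / 15% | 26.3% / 29.4% | +3.1 points | about 15% |
| 10% / 20% | 27.8% / 31.3% | +3.5 points | about 17% |

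With a true 34% against 25%:

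- Equal 10% discard reports 0.34/0.90 − 0.25/0.90 = 37.8% − 27.8% = 10.0 points in place of 9.0.
- The reverse imbalance (15% of usual practice, 5% of the phase arm) reports 35.8% against 29.4%, or 6.4 points, and power falls to about 44%.

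**The case against.** Several points on the other side have force.

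- **The missing-data plan is not emptied.** A reader might infer that {20c} has nothing left to work on. If failure at both times is meant, people missing only week 1 stay, and the scenarios, the interaction calculation and imputation still have cases. This stands.
- **Those removed do not all lack the primary outcome.** A reader might take that as true by definition. It is true only if failure at both times is meant. If either suffices, some of those removed have a valid day-7 result. Withdrawers may also have one.
- **Deletion is not the sole source of the bias.** The wording of {20c} about missing data causing exclusion suggests that the primary logistic model uses complete cases. People with no day-7 outcome would then drop out of it whether or not their records were kept, and most of the tabulated bias would arise anyway. This stands. What deletion itself adds is the loss of day-7 results already obtained and of the material for sensitivity analysis and imputation.
- **The larger examples exceed the forecast.** The article expects under 5% missing. Within that range the effect is small, as the 2.5%/5% row shows. But deleting records would make the forecast hard to check from the retained data.
- **No difference by arm is expected.** The section on discontinuing interventions {11b} says so, because the treatment is the same in all groups. A reader might instead infer that the phase arms will lose more people because they wait longer. The article says only that some participants may have to wait for their next cycle; a link from waiting to discard is a further assumption. Even so, equality cannot be taken for granted, since quit-date timing differs by arm and the trial is open-label.

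**Conclusion.** The point holds. The two discard rules are stated plainly, nothing elsewhere in the article cures them, and they conflict with {19}, with {20c} and with the promise in {18b} itself to account for missing data. Followed as written, they lose data irreversibly, including valid day-7 results of people who withdraw later. They remove the cases that the sensitivity analyses most need and leave the 10% trigger open to being judged on a reduced sample.

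The size and direction of bias are not known. Under the stated assumptions, the rows above run from no distortion of type I error when loss is equal (with inflated quit rates), through about 5.5% at 2.5%/5%, to about 15% at 5%/15%. The opposite imbalance would hide a real benefit. The premise that everyone discarded is not abstinent also fails for any withdrawer with a confirmed abstinent day-7 result, whose deletion would lower the observed rate. The figures therefore show what could happen. They do not support a claim that the trial is biased towards the phase arms, or that deletion alone would produce a 15% type I error.

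**What to change.** 1. Strike both rules under which data are not retained. Keep everything collected from every randomised participant unless that person expressly asks for erasure, and report erasures by arm.
2. State that all randomised participants are analysed in their assigned arm, using any day-7 result already obtained, whatever happens later.
3. Record failure to complete the week 1 or week 6 assessments as a missing outcome, not as removal. This also settles the ambiguity over weeks 1 and 6.
4. State one rule for a missing day-7 outcome that applies alike to non-responders and erased participants. It could count them as not confirmed abstinent, or use multiple imputation whatever the percentage missing. Merely sending non-responders to {20c} as it stands would not be enough, because imputation there starts only at 10%.
5. Run the scenarios and the interaction calculation in {20c} on the full randomised sample, with all randomised participants as the denominator for any percentage.
6. Reconcile {18b}, {19} and {20c}.

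The cost is protocol and consent wording, with slightly lower reported quit rates if a missing outcome is counted as not abstinent. With all 1200 analysed, and the 25% and 34% taken as rates over all randomised, power stays at the 79.8% reproduced above.
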